## Abstract

**Background:** Intensive speech-language therapy (SLT) can promote recovery from chronic post-stroke aphasia, a major consequence of stroke. However, effect sizes of intensive SLT are moderate, potentially reflecting a physiological limit of training-induced progress. Transcranial direct current stimulation (tDCS) is an easy-to-use, well-tolerated and low-cost approach that may enhance effectiveness of intensive SLT. In a recent phase-II randomized controlled trial, 26 individuals with chronic post-stroke aphasia received intensive SLT combined with anodal-tDCS of the left primary motor cortex (M1), resulting in improved naming and proxy-rated communication ability, with medium-to-large effect sizes.

**Aims:** The proposed protocol seeks to establish the incremental benefit from anodal-tDCS of M1 in a phase-III randomized controlled trial with adequate power, ecologically valid outcomes, and evidence-based SLT.

**Methods:** The planned study is a prospective randomized placebo-controlled (using sham-tDCS), parallel-group, double-blind, multi-center, phase-III superiority trial. A sample of 130 individuals with aphasia at least 6 months post-stroke will be recruited in more than 18 in- and outpatient rehabilitation centers.

**Outcomes:** The *primary* outcome focuses on communication ability in chronic post-stroke aphasia, as revealed by changes on the Amsterdam-Nijmegen Everyday Language Test (A-scale; primary endpoint: 6-month follow-up; secondary endpoints: immediately after treatment, and 12-month follow-up). *Secondary* outcomes include measures assessing linguistic-executive skills, attention, memory, emotional well-being, quality of life, health economic costs, and adverse events (endpoints: 6-month follow-up, immediately after treatment, and 12-month follow-up).

**Discussion:** Positive results will increase the quality of life for persons with aphasia and their families while reducing societal costs. After trial completion, a workshop with relevant stakeholders will ensure transfer into best-practice guidelines and successful integration within clinical routine.

**Clinical Trial Registration:**
www.ClinicalTrials.gov, identifier: NCT03930121.

## Introduction

Cerebrovascular diseases are among the most common causes of disability worldwide, and about one third of stroke survivors initially suffer from communication disorders, including aphasia (1). In up to 40% of these individuals, symptoms of aphasia persist 6 months after stroke and rarely recover spontaneously in the ensuing time (2). Critically, chronic post-stroke aphasia affects vocational reintegration, social life, and emotional well-being while placing major burdens on the healthcare system (3).

Meta-analyses concluded that intensive speech-language therapy (SLT) can be effective even in the chronic stage of symptoms (4). In a multi-center randomized controlled trial (RCT), persons with chronic post-stroke aphasia were randomly assigned to either 3 weeks of intensive SLT or a waiting period prior to treatment (5). Verbal communication improved after intensive SLT, but not after the waiting period, as assessed by the Amsterdam-Nijmegen Everyday Language Test (ANELT) (6). The study revealed an average increase of three points on the ANELT (A-scale) immediately after intensive SLT, a relative difference amounting to ~10% (between-group effect: Cohen's *d* = 0.58).

Motivated by a lack of data identified in systematic reviews (7), several proof-of-concept studies provide evidence suggesting that transcranial direct current stimulation (tDCS) is an easy-to-use, well-tolerated, and low-cost approach to boost the effectiveness of SLT in chronic post-stroke aphasia (8). Most of these studies are small-to-medium phase-II trials, with naming ability (9) or other linguistic skills as primary outcomes, but no parameters reflecting everyday life (7), or with individually determined stimulation not feasible for standard application (9–11). Moreover, most of the studies did not assess training effects over extended periods of time.

Our group recently published the first prospective randomized placebo-controlled (using sham-tDCS), parallel-group, double-blind, single-center, phase-II superiority trial on intensive naming therapy combined with anodal-tDCS of the left primary motor cortex (M1), including a sample of 26 persons with post-stroke aphasia, a 6-month follow-up, and outcomes relevant to everyday life (12). Results indicated significantly improved naming and proxy-rated communication ability in both groups. However, treatment gains for trained items were significantly better maintained in the anodal-tDCS group at the 6-months follow-up (Cohen's *d* = 1.19). Importantly, progress in communication ability was significantly higher with anodal-tDCS than with sham-tDCS at all endpoints (Cohen's *d* = 0.75–0.99).

In summary, preliminary data suggest that anodal-tDCS can benefit naming and communication ability in chronic post-stroke aphasia, with medium-to-large effect sizes and long-term stability of treatment gains. To ensure transfer of the intervention to best-practice guidelines and successful integration within clinical routine, a phase-III RCT is needed with adequate power, ecologically valid outcomes, and evidence-based SLT (5).

## Materials and Methods

### Design

The planned study DC-TRAIN-APHASIA (transcranial direct current stimulation to enhance training effectiveness in chronic post-stroke aphasia) is a prospective randomized placebo-controlled (using sham-tDCS), parallel-group, double-blind, multi-center, phase-III superiority trial.

### Patient Involvement and Ethics Approval

Patients, relatives, and their representatives were given the opportunity to discuss the study protocol and utter concerns not addressed in a draft proposed at the time. It was pointed out that in- and exclusion criteria should reflect realistic routine-healthcare conditions; we followed this advice, whenever possible. The final protocol was approved by the Ethics Review Board of the University Medicine Greifswald, Germany (reference number: BB-013/18). Written informed consent will be obtained from each participant. All study procedures are in accordance with the Declaration of Helsinki in its current version (for details, see www.wma.net).

### Recruitment and Setting

Individuals with chronic post-stroke aphasia will be recruited in more than 18 in- and outpatient rehabilitation centers throughout Germany (for an updated list of study sites, see record on ClinicalTrials.gov; identifier: NCT03930121). A similar network of rehabilitation centers proved to be time- and cost-effective in a previous large-scale RCT with long-term follow-ups (5).

### In- and Exclusion Criteria

*Inclusion criteria* are: Left-hemisphere cortical or subcortical stroke with first-ever aphasic symptoms; at least 6 months post-onset of stroke; fluent or non-fluent aphasia, as determined by the Aachen Aphasia Test (AAT) (13); moderate-to-severe word finding difficulties (maximum of 60% correct items on a computerized naming task before treatment); at least one correct reaction on the first part of the AAT subscale Token Test (ensuring basic comprehension skills); at least one point on the communicative task of the AAT subscale Spontaneous Speech (ensuring basic communication abilities); German as first language; age range 18–70 years; and intact left-hemisphere “hand knob” and underlying white matter (for placement of anode), as well as intact right-hemisphere prefrontal cortex (for placement of cathode), to rule out stimulation of lesioned areas, as confirmed by magnetic resonance imaging (MRI) or computer tomography (CT) scans.

*Exclusion criteria* are: Contraindications for tDCS (e.g., cardiac pacemaker, history of seizures, implanted metal inside the head); more than one clinically apparent stroke with aphasic symptoms, as documented by clinical records and MRI or CT scans of the brain; other severe neurological diseases, as assessed by an independent neurologist (e.g., epilepsy, brain tumor, subdural hematoma); psychiatric conditions that may impair effective communication, as evaluated by an independent clinical psychologist or psychiatrist according to the DSM-5 system: current diagnosis of severe alcohol or substance use disorder (at least six out of eleven symptoms), current major depressive episode (at least five out of nine symptoms, among them depressed mood or anhedonia), and current disorder from the psychotic spectrum (at least two out of five symptoms, among them delusions, hallucinations or disorganized speech) (14); severe apraxia of speech, as revealed by Hierarchical Word Lists (<20% phonetically and phonematically correct items) (15); severe non-verbal cognitive deficits, as demonstrated by the Corsi Block-Tapping Task (less than four correct items) (16); severely impaired vision or hearing that prevents individuals from engaging in intensive SLT based on clinical experience; and changes in centrally active drugs within 2 weeks prior to study inclusion.

### Randomization

In addition to intensive SLT, participants will either receive anodal-tDCS or sham-tDCS, depending on group assignment (allocation ratio of 1:1). Groups will be stratified-randomized according to age (<60 vs. ≥ 60 years), aphasia severity at baseline (AAT *t*-score classification at screening: severe vs. mild-to-moderate aphasic symptoms), and center (for details, see Figure 1). Block randomization will be used (randomly varying block sizes of 4 and 6).

**Figure 1 F1:**
[figure not shown]
Trial flow. SLT, Speech-language therapy; tDCS, transcranial direct current stimulation; ANELT, Amsterdam-Nijmegen Everyday Language Test (A-scale).

### Behavioral Treatment, Stimulation, and Blinding

In the planned RCT, participants will receive intensive treatment (5) consisting of computer-assisted naming therapy (12) and face-to-face communicative-pragmatic therapy (17). Treatment will be tailored to the participants' individual needs. For naming therapy, personally relevant items will be chosen in a baseline screening to reflect individual language ability, a procedure previously described and established in a phase-II RCT (12). For communicative-pragmatic therapy, training tasks of individual complexity will be identified in an extensive baseline screening (18). These tasks will include a variety of situations known from everyday life that require verbal and non-verbal skills in context of social interaction (17). Treatment will be administered in two daily sessions over a period of three consecutive weeks (2 h of daily naming therapy; 30 min of daily communicative-pragmatic therapy; total weekly dosage: 12.5 h). During the entire 3-week treatment period, participants will not attend any other form of SLT.

Intensive SLT will be combined with tDCS using a battery-driven device (DC-Stimulator Plus, NeuroConn, Ilmenau, Germany). The anode (5 × 7 cm^2^) will be placed horizontally over the left M1 representation of the hand (C3 of the 10–20 international EEG system) (12, 19). A functionally inert cathode (10 × 10 cm^2^) will be positioned over the right supraorbital region. In the *Intervention Group*, participants will receive 20 min of excitatory anodal-tDCS of M1 administered at the beginning of each session. In the *Control Group*, the current will be ramped up and remain at 1 mA only for 30 s prior to ramping down. This sham-tDCS does not affect neural activity, but ensures blinding of participants due to initial tingling sensations on the scalp, and therefore is the comparator of choice consistent with previous work (12, 19). Participants and therapists will be blinded to group assignment by using the “study mode” of the stimulator, a masked randomization procedure determined by algorithms. The randomization sequence will be encrypted and stored on a secure server. Crucially, participants and therapists will be unaware of the group assignment throughout the entire study. To further increase blinding integrity, data evaluation will be performed by an independent Endpoint Committee blinded to group assignment and time of assessment.

### Hypotheses

The *primary hypothesis* predicts that intensive SLT combined with anodal-tDCS leads to better communication ability than intensive SLT combined with sham-tDCS. Likewise, *secondary hypotheses* predict favorable scores on secondary outcomes with anodal-tDCS compared to sham-tDCS (for details, see Table 1). *Primary endpoint* will be a 6-month follow-up; *secondary endpoints* will be immediately after treatment, and a 12-month follow-up. The 6-month follow-up as primary endpoint is assumed to reflect the impact of symptom recovery on aspects of everyday life most adequately and proved to be particularly sensitive to the effect of anodal-tDCS in previous work (12). The 12-month follow-up will help explore the long-term stability of the expected results.

**Table 1 T1:** Testing.

**Study procedure**	**Pre-screening**	**Screening**	**Baseline**	**Treatment**	**Post-treatment**	**6-month follow-up**	**12-month follow-up**
**Visit number**			**T**_**0**_		**T**_**1**_	**T**_**2**_	**T**_**3**_
**Place**	**Clinic**	**Clinic/patients' home**	**Clinic/patients' home**	**Clinic**	**Clinic/patients' home**	**Clinic/patients' home**	**Clinic/patients' home**
Study month			0	Week 1–3	1	6	12
Informed consent	•						
In- and exclusion criteria (chart-based)	•						
In- and exclusion criteria (study-specific)		•					
Demographics and medical history		•					
Prior and current treatment		•					
Vital signs				•			
Physical examination				•			
Magnetic resonance imaging		•					
Aachen Aphasia Test		•				•	
Hierarchical Word Lists		•					
Corsi Block-Tapping Task		•					
Amsterdam Nijmegen Everyday Language Test			•		•	•	•
Naming ability		•			•	•	•
Communicative- Pragmatic Screening			•				
Scenario Test			•			•	
Communicative Effectiveness Index			•		•	•	•
NeuroCogFX			•			•	
Benton Visual Retention Test			•			•	
SADQH-10			•		•	•	•
SAQOL-39g			•		•	•	•
EQ-5D-5L and EQ-5D-VAS			•		•	•	•
Patient Resource Consumption Questionnaire			•			•	•
Burden of informal caregivers			•		•	•	•
tDCS Safety Questionnaire			•	•	•	•	•
Minimal Important Difference					•	•	•

*Selected linguistic functions, Aachen Aphasia Test (13); Apraxia of speech, Hierarchical Word Lists (14); Non-verbal working memory, Corsi Block-Tapping Task (15); Communication ability (primary outcome), Amsterdam Nijmegen Everyday Language Test (A-scale; parallel versions used in counterbalanced order across participants) (6); Naming ability, personally relevant trained and untrained items, consistent with previous work (12); (Non-)verbal communication, Communicative-Pragmatic Screening (18), Scenario Test (Nobis-Bosch et al. in preparation), and Communicative Effectiveness Index (20); Attention and executive function, reaction-speed subscales from NeuroCogFX (21); Non-verbal episodic memory, Figure Recognition Task from Benton Visual Retention Test (22); Mood, German version of the 10-item Stroke Aphasic Depression Questionnaire (SADQH-10) (23); Health-related quality of life, SAQOL-39g (24); EQ-5D-5L and EQ-5D-VAS (25); Health economic evaluation: direct and indirect costs during the 12-month study period (determined by the self-developed Patient Resource Consumption Questionnaire and based on common standardized unit cost assumptions), and Quality-Adjusted Life Years (derived from the EQ-5D-5L data) (26); Unpaid support provided by family members or friends, Burden of informal caregivers (27); (Serious) adverse events, tDCS Safety Questionnaire (28); Subjective treatment-induced change, as experienced by patients, therapists, and relatives, Minimal Important Difference (29)*.

### Primary Outcome

Communication ability in 10 everyday-life situations will be evaluated by parallel versions of the ANELT (A-scale) (6). ANELT has good psychometric properties, including high test-retest reliability and sensitivity to treatment-induced progress in chronic post-stroke aphasia (2, 5). Each testing session will be videotaped and scored offline by the external Endpoint Committee.

### Secondary Outcomes

*Secondary* endpoints include measures representing linguistic-executive skills, attention, memory, emotional well-being, quality of life, health economic costs, and adverse events (for details, see Table 1).

### Sample Size Estimates

We expect a between-group difference on the ANELT of at least three points at the 6-month follow-up. An independent-sample *t*-test with a two-sided significance level of 0.05 has a power of 80% to detect an average between-group difference of 3.0 points (standard deviation: 5.8) at the 6-month follow-up if data from 120 participants are analyzed, according to calculations using nQuery with raw data from previous work (12). Assuming a drop-out rate of 10%, 130 individuals will be recruited. Determining samples sizes with *t*-tests is a conservative approach: the planned analysis of covariance (ANCOVA) with (1–*p*^2^) × *n* participants has the same power as a *t*-test with *n* participants, where *p* is the variance deflation factor, calculated by the correlation of baseline and follow-up measures (30). In the worst case of *p* = 0, the resulting sample size corresponds to a *t*-test.

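### The figures 120 analysed, 10% drop-out and 130 recruited do not fit together: 130 allows for 7.7% drop-out, and 10% would leave 117 (a minor error)

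*Protocol article*

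**What the plan says.** The section Sample Size Estimates of the protocol article bases the size on an independent-sample t-test, two-sided at 0.05. It assumes an "average between-group difference of 3.0 points (standard deviation: 5.8) at the 6-month follow-up", and the stated power of 80% holds "if data from 120 participants are analyzed". The allowance for losses follows directly: "Assuming a drop-out rate of 10%, 130 individuals will be recruited". The Abstract repeats the target: "A sample of 130 individuals with aphasia at least 6 months post-stroke will be recruited". The Randomization section gives an "allocation ratio of 1:1".

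Sample Size Estimates then describes the t-test sizing as conservative, because the planned analysis is an ANCOVA. It gives (1 − p²) × n as the number that an ANCOVA needs to match a t-test with n participants, where p comes from the correlation of baseline and follow-up. It names p = 0 as the worst case. Statistical Analyses plans an intention-to-treat analysis of the whole group, with multiple imputation of missing values where appropriate.

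**The concern.** A drop-out allowance has one job: after the assumed loss, the number that the power statement needs should still be there. Here the analysed number, the loss and the recruitment target stand in adjacent sentences, and one division shows that the third does not follow from the first two. This is the sample-size justification of a phase-III trial that claims adequate power, and the figures are likely to be repeated in the main report. At stake is whether that justification is correct as printed and, to a small extent, the power that can be quoted for the assumed loss.

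**Working it through.** **Inputs** (all from Sample Size Estimates, except the 1:1 allocation from Randomization): difference 3.0 ANELT points; standard deviation 5.8; two-sided 0.05; 120 analysed; 10% drop-out; 130 recruited.

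**Step 1: reproduce the 120.** For a two-sample t-test the noncentrality is 3.0 / [5.8 × √(1/n₁ + 1/n₂)].
- 60 and 60: 3.0 / (5.8 × √(2/60)) = 3.0 / 1.059 = 2.83. The noncentral t-distribution with 118 degrees of freedom gives power 80.2%.
- 59 and 59: power 79.6%.

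So 60 per arm is the smallest balanced size that reaches 80%. The protocol's 120 and its 80% both reproduce.

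**Step 2: try to reproduce the 130.**
- Inflation for a loss of 10%: 120 / (1 − 0.10) = 133.3, so 134 (67 per arm).
- The common but incorrect shortcut: 120 × 1.10 = 132.

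Neither gives 130.

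**Step 3: work forward from 130.**
- 130 × (1 − 0.10) = 117 with observed 6-month data, which is 3 fewer than 120.
- Drop-out at which 130 leaves exactly 120: 1 − 120/130 = 10/130 = 7.7%.

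**Step 4: the effect on the t-test.** With 58 and 59, the noncentrality is 3.0 / (5.8 × √(1/58 + 1/59)) = 3.0 / 1.072 = 2.80, and power is 79.2%. The difference detectable with 80% power becomes 3.03 points, against the 3.0 assumed.

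**Step 5: the protocol's own ANCOVA argument.** An ANCOVA with 117 matches a t-test with 120 when (1 − p²) × 120 = 117. That gives p² = 1 − 117/120 = 0.025, so p = 0.16. This assumes that 5.8 is the standard deviation of follow-up scores; the text does not say which standard deviation it is. The protocol gives no correlation, so a range is shown for 117 participants:

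| Assumed correlation | Power |
|---|---|
| 0 | 79.2% |
| 0.1 | 79.6% |
| 0.2 | 80.8% |
| 0.3 | 82.8% |
| 0.5 | 89.3% |

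**The case against.** The best defence is that nothing of substance follows. The t-test is only the worst case, and the planned analysis is the ANCOVA. The section Primary Outcome credits the ANELT with high test-retest reliability, so a correlation near zero is implausible. If 5.8 were instead the standard deviation of change scores, then with equal variances at baseline and follow-up the ANCOVA variance is (1 + p)/2 times the change-score variance. The gap is then covered whenever (1 + p)/2 is at most 117/120 = 0.975, that is, for any correlation up to 0.95. The argument would fail only if 5.8 were already a residual standard deviation after adjustment for baseline, which the text does not suggest. In addition, 10% is itself a round planning assumption, and 7.7% lies close to it.

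All of this stands as a limit on the consequence. It does not make the figures agree, because the protocol offers the ANCOVA as a reason for calling the sizing conservative and not as the basis for the 130.

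Two other defences are weaker. The 130 may come from a normal approximation: about 117.3 before rounding, and 117.3/0.90 = 130.4. The text does not state that route. It states 120, and by the exact t-test 117 falls just short of 80%. Multiple imputation may bring all 130 into the analysis, which is why 117 should be described as the number with observed 6-month data and not as the number analysed. Imputation does not generally restore the information lost with missing outcomes.

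In the other direction, a reader might infer that the trial fails to deliver its stated power, or that adjusting for centre makes the shortfall worse. The documents support neither. The first overlooks the ANCOVA argument in the same section. For the second they give no figures from which such a loss could be calculated.

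**Conclusion.** The point holds as a minor error. The stated combination of 120, 10% and 130 is wrong as written. The gap is 3 participants with 6-month data, or 4 at recruitment, and about one percentage point of t-test power (79.2% against 80.2%). That inconsistency rests only on the protocol's printed figures. The conclusion that the consequence is small rests on the planned ANCOVA and, for the threshold of 0.16, on 5.8 being the standard deviation of follow-up scores. The finding does not show that the trial is materially underpowered.

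**What to change.** Correct the drop-out sentence in Sample Size Estimates without enrolling more participants. Either of these would do:

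- *Recruiting 130 allows for a drop-out of 7.7% while retaining 120 participants with 6-month data.*
- *With 10% drop-out, 117 of 130 participants have observed 6-month data, and the t-test has 79% power before any gain from ANCOVA.*

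The first is the simpler, since it leaves the 120 and the 80% as they are. The second should not say that 117 are analysed, because that would conflict with the intention-to-treat analysis and multiple imputation in Statistical Analyses. The 130 in the Abstract can stay. The cost is wording only: design, enrolment and analysis are unchanged. The first option states a smaller allowance for losses, and the second states a power about one percentage point lower.
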